### 8.1.5 Study-drug delivery & drug storage conditions

Hydroxychloroquine, lopinavir and ritonavir, remdesivir and RAS blocking agents are all approved substances that are stored and released by the central pharmacy of each trial center.

Asunercept will be provided for 300 patients (100 for each dose group) by Apogenix AG.

Pentaglobin is an approved substance that is stored and released by the central pharmacy of each trial center.

### 8.1.6 Study drug packaging and labeling

This is an open label trial. Medication will therefore not be labelled.

### 8.1.7 IMP administration & handling

All trial substances should be handled and administered according to manufacturer's recommendations. Tablets/pills may be broken or crushed and administered via nasogastric tubes.

### 8.1.8 Drug accountability

All medication for the open label trials will be dispensed by the local central hospital pharmacies. Drug Accountability will be recorded at on-going basis on paper form/source data. Drug dispensing to patients (e.g. early discharge) have to be entered into the CRF. Furthermore, the correct intake of IMP or any variations concerning that will be recorded in the (e)CRF at each visit during treatment period.

### 8.1.9 Procedures to assess subjects compliance

For "antiviral" treatment arms and sub-studies only hospitalized patients will be included and intake of peroral medication will be controlled. In sub-study C all substances will be administered intravenously, therefore therapy adherence will not be an issue. In substudy B, in case of a discharge, patients will receive the required medication for the full treatment course.

### 8.1.10 Concomitant medication

The treatment for SARS-CoV-2 infection will not interfere with other treatment of patients and the treating physicians may decide upon concomitant medication without limitations. Noteworthy, the interaction potential of some substances, especially ritonavir, is remarkable and this should be kept in mind when treating these patients.

**Allowed:** in general, concomitant treatment is allowed and will be decided upon by treating physicians, best standard of care, according to local standards

**Not allowed:** Contraindication of the specific experimental treatments (according to their summary of product characteristics) have to be **considered by treating physicians**

## 8.2 Randomization and stratification

This is a randomized trial with different active treatments. However, for this platform trial, some special circumstances need to be considered. In the “Main” antiviral study three treatment options remain active within the randomized trial. Sub-study A, B, C, will also be conducted as randomized trials against standard of care. Randomization will be carried out online by [www.meduniwien.ac.at/randomizer](http://www.meduniwien.ac.at/randomizer). No stratification will be applied, except for the asunercept part of the trial. Based on the currently known risk factors, hospitalized patients are probably older and have more comorbidities, compared to a “general population”. Moreover, the sample sizes are relatively small, which precludes further stratification due to statistical reasons.

For sub-study B randomization will occur within the treatment group. In this cohort (labelled as “sub-study B”), patients with established arterial hypertension (and treatment) may be switched and patients with blood pressure  $\geq 130/85$  mmHg will be randomized to new treatments. Importantly, those patients with blood pressure  $\geq 130/85$  mmHg but  $< 140/90$  mmHg, who are randomized to non-RAS blocking treatment will not receive any treatment. Patients will be randomized to the following two treatment options using an allocation ratio of 1:1

- RAS blocker containing treatment (candesartan)
- Non-RAS blocker containing treatment (e.g. nitrendipin/amlodipin/doxazosin)

Thus, clinicians may decide within the first 24 hours if patients who participate in the main antiviral study A will also fulfill the criteria for one of the sub-studies. It is currently not intended to simultaneously enroll a patient in sub-studies A or B. Within sub-studies randomization will be done using the same software.

For sub-study C:

Asunercept: a 3:1 randomization against standard of care will be done, whereas three different doses of asunercept will be tested. Stratification according to the WHO scale at screening will be performed (only WHO scales 4, 5, and 6 are available for inclusion (patients with oxygen demand).

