|  | 
Sub-Study A Anticoagulation: Patients with eGFR of >20 mL/min will be randomized to treatment with rivaroxaban or standard of care which likely includes prophylactic doses of low molecular weight heparins.
 
Sub-Study B RAS Blockade: Patients with blood pressure <math>\geq 130/85</math> mmHg (or established and treated arterial hypertension) may be included into a sub-study labeled as B. The decision whether to include patients also in sub-study B will be taken within the first 24 hours after randomization to the main study. Two consecutive blood pressure measurements are a prerequisite for randomization. Patients in the sub-study B will be randomized to two groups with different antihypertensive treatment: RAS-blocker containing treatment (candesartan) and non-RAS-blocker containing treatment (e.g. nitrendipine, doxazosin). We expect that about 1/3 of patients in the main part might also be included in sub-study B. Additionally, two control groups will be included: control group 1 will consist of patients with suspected COVID-19 infection, who test negatively for SARS-COV-2 infection (n=10) and healthy volunteers with negative tests for SARS-COV-2 (n=10)
 
Sub-Study C Anti-inflammatory/Immunomodulatory treatment: patients may be eligible for experimental anti-inflammatory treatment. In short, in this randomized sub-study hospitalized patients with clinical or radiological signs of pneumonia and oxygen demand may be included. These patients are at increased risk to develop a severe cause or fatal disease. Thus, they may receive asunercept, a fully human CD95L-binding protein, or pentaglobin, IgM enriched immunoglobulins. This part of the study will be randomized against standard of care. This part of the study may include patients who were also included into sub study A and/or B. For the asunercept part of sub-study C, four treatment groups will be available: one control arm (standard of care) and three different dose groups (25mg, 100 mg and 400 mg per week i.v.). randomization will be carried out in 1:3 ratio. Initially, inclusion of 100 patients is planned, although, the final sample size will be determined during interim analyses (see detailed information in the statistical analysis part). For the Pentaglobin part of sub-study C the primary objective is the inclusion of patients with uni-/bilateral pneumonia, elevated C-reactive protein levels (>5 mg/dl) and respiratory deterioration in danger of sepsis or acute respiratory distress syndrome (ARDS) who are admitted to an ICU.
 |

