| 
COMPARATIVE
/CONTROL CONDITION
 | 
DRUG
 
Main Study:
Different “antiviral” treatment arms will be tested against each other and against SOC
 
Sub-study A:
Randomization will be carried out against standard of care which will likely include prophylactic doses of low molecular weight heparin.
 
Sub-study B:
randomized switch of patients with previously known and treated hypertension to non-RAS blocking agents (standard of care, e.g. nitrendipine, amlodipine or doxazosin) versus “stay-on-any-RAS-blockade”, or de novo treatment of patients with blood pressure >130/85mmHg in two consecutive measurements with RAS blocking agent (candesartan) versus non-RAS-blocking agents (e.g. nitrendipine, amlodipine or doxazosin), or no treatment, if blood pressure <140/90mmHg. RAS blockers will be compared vs. non-RAS blocking antihypertensive agents.
Healthy volunteers as another control group
 
Sub-study C:
Asunercept: Randomization will be done between groups receiving Asunercept at different dose levels (group 1: 25 mg; group 2: 100 mg; group 3: 400 mg) and best standard of care. Thus, there will be a 3:1 randomization between patients receiving verum and control patients. In case of a safety signal at interim analyses at a given dose, the arm will be terminated and patients will be switched to the remaining dose(s) which is/are tolerated. In case differences in efficacy are seen at interim analyses, patients will be switched from the less effective dose(s) to the more effective dose(s) or to equally effective lower dose(s)
 
Pentaglobin: Randomisation will be carried out against best standard of care (without IVIG or IL-6 blockage).
 |

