### 7.1.2 Inclusion criteria

- Laboratory confirmed (i.e. PCR-based assay) infection with SARS-CoV-2 (ideally but not necessarily  $\leq 72$  hours before randomization for “antiviral” treatments) OR radiological signs of COVID-19 in chest X-ray or computed tomography
- Hospitalisation due to SARS-CoV-2 infection, except for sub-study B, which may also include outpatients with COVID-19
- Requirement of oxygen support (due to oxygen saturation  $<94\%$  on ambient air or  $>3\%$  drop in case of chronic obstructive lung disease)
- Informed Consent obtained, the patient understands and agrees to comply with the planned study procedures, except for sub-study C: obtaining informed consent may be impossible due to the severe condition of the patient and may be waived
- $\geq 18$  years of age
- Sub-study A: not on chronic anticoagulation
- Sub-study B: Sub-study B: blood pressure  $\geq 130/85\text{mmHg}$  in 2 consecutive measurements OR patients with established and treated hypertension
- Sub-study B: Control group 1: Patients with suspicion of but negative tests for COVID-19. This group may consist of hospitalized and non-hospitalized patients.
- Sub-study B: healthy volunteers
- Sub-study C: Signs of respiratory deterioration and progressing inflammation: need for oxygen supplementation, non-invasive ventilation, high-flow oxygen devices or mechanical ventilation AND CRP levels  $>5\text{mg/dL}$  (for Pentaglobin only) and ICU admission (for Pentaglobin only)
- For female patients with childbearing potential: willingness to perform effective measures of contraception during the study.

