#### **Sub-Study B: RAS blockade**

Initial dose: candesartan 8 mg 1-0-0; (compared to standard of care, e.g. nitrendipin 10 mg 1-0-1, amlodipine 5mg 1-0-0 or doxazosin 2 mg 1-0-1)

Maintenance dose: Uptitration to normotension

Route of administration: p.o.

Duration: Through recovery, unless discontinuation is necessary for clinical reasons

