#### ADJUNCTIVE THERAPIES

Randomization to one of the adjunctive therapies is desirable but not necessary. To make it more feasible, it is recommended that eligibility for adjunctive therapies is discussed during daily ward rounds.

For sub-study A patients who are not on chronic oral anticoagulation are eligible.

For sub-study B only hypertensive patients (>130/85mmHg) are eligible. Those patients with established arterial hypertension and antihypertensive treatment will be randomly switched to non-RAS-blocking therapy (e.g. nitrendipine or doxazosin, depending on comorbidities and concomitant medication) versus "stay-on-any-RAS-blockade". Patients with previously undiagnosed arterial hypertension will receive candesartan, as RAS blocking agent, and a non-RAS-blocking agent as standard of care (e.g. nitrendipine, amlodipine or doxazosin, depending on comorbidities and concomitant medication). Treating physicians will titrate the dose to normotension and may add other non-RAS blocking therapy if the maximum dose of the chosen antihypertensive medication does not suffice. RAS-fingerprint will be measured at the same timepoints. In case of an early discharge, RAS fingerprint will be measured at least once weekly (i.e. on days 7±1, 14±1, 21±1, 28±1, through recovery).

Additional analysis of local RAS activity in the lung will be performed in bronchoalveolar lavage samples in case of clinically indicated bronchoscopy or lung tissue following autopsy. End-of study visit will be performed after full recovery.

For asunercept the treatment will be administered once per week intravenously up to four weeks, or until hospital discharge or death, whichever occurs first. The clinical endpoints (including WHO ordinal scale,

NEW Score, oxygenation, etc.) will be obtained on a daily basis during visitation or until death or hospital discharge. Blood pressure, heart rate, respiratory rate, oxygen demand, oxygen saturation, mode of oxygen delivery, concomitant medication and radiologic changes regarding CXR/CT/lung ultrasound are documented as part of routine care. Laboratory analyses (similar to screening investigation) including c-reactive protein, D-Dimer, IL-6 and troponin levels will be performed three times a week, and in case of clinical necessity possibly more often.

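### For previously treated hypertensives, the protocol defines the RAS-blockade arm of sub-study B in conflicting ways, and its entry wording conflicts too, so one allocation can mean different treatments

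*Protocol*

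**What the plan says.** The protocol describes the active arm of sub-study B in three ways.

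- **Candesartan only.** Section 8.2 states "Patients will be randomized to the following two treatment options using an allocation ratio of 1:1" and lists the active option as "RAS blocker containing treatment (candesartan". On patients already treated it says only that "patients with established arterial hypertension (and treatment) may be switched", without saying to what or in which arm. The synopsis entry on patients and groups has "RAS-blocker containing treatment (candesartan) and non-RAS-blocker containing treatment". The synopsis entry on the investigational drug, section 8.1.1 ("Initial dose: candesartan 8 mg 1-0-0") and the sub-study B comparison at the end of section 11.6.2 also name candesartan alone.
- **Continue or start, by history.** The synopsis comparator entry, section 6.2 and section 8.5.3 give previously treated patients "stay-on-any-RAS-blockade" in the RAS arm and a switch to non-RAS agents in the other. Candesartan is kept for patients starting treatment.
- **Three groups.** The sub-study B item in the secondary-endpoint list of section 11.6.2 refers to patients randomised to no RAS blocker, to an ACE inhibitor, and to angiotensin II blockade.

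Entry is described in two ways. Section 7.1.2 and the synopsis accept a pressure of at least 130/85 mmHg on two readings "OR patients with established and treated hypertension". The second route requires neither a RAS blocker nor a pressure level. Sections 7, 7.1.1 and 8.5.3 limit the sub-study to patients with pressure above 130/85 mmHg.

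**The concern.** The randomised comparison in sub-study B is defined by what a patient allocated to RAS blockade receives and what a patient allocated to the other arm receives. For someone already on antihypertensive treatment, the answer depends on which section the site follows. Two sites could treat identical patients differently under the same allocation, both in line with the protocol.

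This is a contradiction about treatment assignment. The separate sub-study SAP promised in section 11 cannot settle it, because an analysis plan does not decide what patients are given. Section 5.2 raises two distinct questions: whether continuing a RAS inhibitor is safe, and whether starting one is beneficial. The continue wording addresses the first and the candesartan wording the second. Without one stated assignment per type of patient, it is unclear which question a treated patient informs. In addition, one combination of the passages allows a patient to be randomised between two arms that do not differ for that patient.

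**Working it through.** No stated figure needs reproducing. The protocol gives a target of 100 patients for sub-study B (section 7.1.1) but no effect size, power or significance level, so the check sets the passages side by side.

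Step 1: list the patients who can enter. The criteria in section 7.1.2 allow three groups: treated with a RAS blocker, treated without one, and untreated with raised pressure.

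Step 2: read off the assignments for each group.

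| Entry group | Section 8.2, read literally | Section 8.5.3 |
|---|---|---|
| Treated, on a RAS blocker | Candesartan versus non-RAS treatment | Stay on own RAS blocker versus switch to non-RAS |
| Treated, on no RAS blocker | Candesartan versus non-RAS treatment | No RAS blocker to stay on; already on non-RAS treatment |
| Untreated, raised pressure | Candesartan versus non-RAS treatment (none if below 140/90 mmHg) | Candesartan *and* a non-RAS agent, as worded |

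Step 3: compare the rows.

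- Row 1. The RAS arm is a specified drug under one wording and the patient's existing drug under the other. A patient on an ACE inhibitor would be changed under the first and left alone under the second.
- Row 2. Section 8.2 gives a contrast and section 8.5.3 gives none. No passage says what this patient receives in the RAS arm under the continue wording.
- Row 3. All sections name candesartan for the RAS arm. The remaining oddity is the conjunction in section 8.5.3: "Patients with previously undiagnosed arterial hypertension will receive candesartan, as RAS blocking agent, and a non-RAS-blocking agent as standard of care". Read literally, that is both agents together, whereas section 8.2 and the synopsis set one against the other.

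Step 4: check whether entry rules close the gap in row 2. The synopsis comparator entry starts candesartan in patients above 130/85 mmHg on two readings and does not say they must be undiagnosed, so it could catch some treated patients on no RAS blocker. Section 8.5.3 ties candesartan to hypertension not previously diagnosed, which excludes them. Treated patients with controlled pressure enter under section 7.1.2 but not under sections 7, 7.1.1 and 8.5.3. The gap therefore opens or closes with the section used.

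Step 5: compare the number of arms. Section 8.2 has two arms at 1:1. The secondary-endpoint list in section 11.6.2 has three groups, with ACE inhibitor and angiotensin II blockade as separate randomised assignments. No randomisation rule in the protocol produces those groups.

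**The case against.** The strongest reply is that much of this is a short label beside a longer description. The sections with the continue rule also name candesartan, for new starters. Section 8.1.1 gives an initial dose, which fits new starters, and section 8.2 itself separates treated patients from those given new treatment. This stands in part: the conflict concerns previously treated patients. A reader might infer that the whole RAS arm is undefined, but the documents do not support that.

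Second, a reader might object that the arm mixes drugs and doses. That is not a fault here. The synopsis comparator entry states the comparison at class level, and section 5.2 makes continuing existing RAS inhibitors a leading question.

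Third, staying on a RAS blocker presupposes taking one, so the rule may never have been meant for patients on other drugs, and the pressure threshold in sections 7, 7.1.1 and 8.5.3 would keep out the controlled ones. This narrows the gap but does not close it. Section 7.1.2 and the synopsis still admit these patients, and section 8.5.3 leaves those above the threshold without an assignment to RAS blockade.

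Fourth, the conjunction in section 8.5.3 is probably a drafting slip. That is accepted, and it carries no weight in the conclusion.

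**Conclusion.** The point holds for previously treated hypertensives. The protocol gives incompatible definitions of their RAS arm, a further three-group scheme that section 8.2 does not provide, and incompatible entry rules. Under the entry wording of section 7.1.2 combined with the continue wording of section 8.5.3, a treated patient taking no RAS blocker can be randomised with no treatment contrast. Under section 8.2 read literally, the same patient has one.

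The size cannot be stated. The documents do not say how many treated patients would enter without a RAS blocker. A reader might infer a definite loss of power or a required increase over the planned 100 patients. Neither follows, because the share is unknown and sub-study B has no stated power to lose. What is established is that the treatment contrast is ambiguous for one class of eligible patients, and this should be corrected.

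**What to change.** - Reconcile the synopsis entries (patients and groups, inclusion criteria, investigational drug, comparator) with sections 6.2, 7, 7.1.1, 7.1.2, 8.1.1, 8.2, 8.5.3 and both places in section 11.6.2. Each entry group (treated with a RAS blocker, treated without one, untreated) should have one stated assignment per arm, or be stated to be ineligible. Which regimen and which entry rule apply is for the sponsor to decide.
- Make the RAS-fingerprint item in section 11.6.2 match the arms actually randomised.
- As a minor wording correction, replace the conjunction in section 8.5.3 with *versus* if that is what is meant.
- Adjust or stratify the sub-study B analysis for RAS-blocker use before randomisation. This separates patients continuing treatment from those starting it. It cannot create a contrast in a group that has none, so the wording must be settled as well.

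The cost is protocol text and one analysis factor. Medication is already recorded at screening (Table 1 and section 11.6.4), so no new data collection is needed.

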**Pentaglobin: randomization against best standard of care will be done.**

## 8.3 Blinding

Not applicable, open label trial.

### 8.3.1 Emergency procedure for unblinding

Not applicable, open label trial.

### 8.3.2 Unblinding at the end of the study

For statistical analysis, unblinding will be performed at interim analyses and at the end of the trial.

## 8.4 Benefit and risk assessment

SARS-CoV-2 is a global pandemic. Current data about its mortality are somewhat diverging and report mortality rates between 1% and 15%, depending on the statistical approach (5). The rapid spread of the disease and the high number of infected patients may cause a breakdown of the healthcare system, which dramatically increased the mortality rate from 1% to 12% in China (6). Similar numbers are expected in Italy. In general, the following risk factors are reported: older age and patients with more comorbidities. However, it is important to note that also young patients without comorbidities may have severe disease courses. To date there is no established, effective treatment. Within the scope of the exponential increase in patient numbers in the current pandemic effective treatments, which possibly reduce the duration of hospitalization or even reduce the number of necessary hospitalizations are of extreme importance to maintain the functionality of the healthcare system within each concerned country. Thus, we believe that the current project may help to answer some important answers in the fight against SARS-CoV-2.

All of the chosen treatments showed promising results *in vivo* or *in vitro*, although data from high quality randomized controlled trials are missing. Hydroxychloroquine, but also lopinavir/ritonavir are already in clinical use, although no data for efficacy from randomized controlled trials are available. These drugs are approved for other diseases and their side effect profile is well-known. For hydroxychloroquine, the risk of clinically relevant arrhythmias needs to be considered. Drug-drug interactions, old age of patients and inflammatory responses may cause relevant changes in the metabolism of both substances, which may cause arrhythmias. QTc monitoring is recommended for these patients, although it may be difficult to perform in isolated patients. If the QTc time is prolonged relevantly during screening, clinicians may exclude patients from this treatment arm. The Department of Clinical Pharmacology may be contacted for an interaction check, if drug-drug interactions are suspected or if clinically indicated. For lopinavir/ritonavir a relatively high-dose was chosen. However, the safety profile is excellent, with mainly gastrointestinal side effects reported in various studies and case reports and available data suggest that higher drug concentrations are necessary.

RAS blockers may alleviate the disease course especially towards ARDS and it is currently unknown whether RAS blockade increases the risk of infection itself. Subjects randomized to RAS blockers treatment are only available for randomization in case of a "high normal blood pressure ( $\geq 130/85$  mmHg) and this treatment should not pose any relevant risks on patients, if started at the lowest available dose. Those with a blood pressure  $< 140/90$  mmHg randomized to the control group will not receive any treatment. Moreover, hospitalized patients will be monitored for blood pressure anyway. The inclusion of ten healthy volunteers and negatively tested patients as another control groups is scientifically

justified and the associated risks seem acceptable. Only blood samples will be drawn and oral/nasopharyngeal virus swabs will be obtained (to prove SARS-COV-2 negativity).

Asunercept might be able to avoid the need for mechanical intubation in COVID-19 patients and also ameliorate the course of disease in patients in need of high oxygen flow devices, which has been shown to be a risk factor for infectiousness due to the creation of virus particle containing aerosol. Importantly, no particular risks were identified associated with Asunercept in the clinical trials in which it has been employed. Therefore, no risk populations are excluded from participation.

Pentaglobin is human IgM enriched immunoglobulin for intravenous use. It contains immunoglobulin G (IgG) and increased concentrations of immunoglobulin A (IgA) and immunoglobulin M (IgM) with a broad spectrum of antibodies against various pathogens of infectious diseases and their toxins.

Pentaglobin contains the antibody spectrum of the normal population. Because of the increased levels of IgA and especially IgM, Pentaglobin has higher titers of agglutinating antibodies against bacterial antigens than pure IgG preparations. Pentaglobin is made from pooled plasma from at least 1000 donors. With suitable doses of this drug, abnormally low immunoglobulin concentrations can be restored to normal. The mechanism of action has not yet been fully elucidated, but includes immunomodulatory effects.

